### Allocation

Computerised block randomisation will take place after the patient has been anaesthetised. Allocation concealment will be assured by using ALEA, a web-based data system supervised by the Clinical Trial Centre of the Erasmus MC. Variable block sizes of 4, 6 and 8 will be used and stratified by treatment centre. Patients will be randomised in a 1:1 ratio to laminectomy or bilateral interarcuair decompression. Each patient will be given a unique study number.

### Blinding

All researchers and patients will be blinded for the treatment. This is possible, because there are no fundamental differences between both procedures (eg, general anaesthesia, spinal incision, inpatient procedure). The statistical analyses will be performed blinded. The surgeon cannot be blinded.

### Data collection methods

All patient reported outcomes will be collected preoperatively and after 3 weeks, 6 weeks, 3 months, 6 months, 12 months, 18 months, 24 months, 36 months and 48 months (see table 1). Patients will receive an email with a link, reminding them of the upcoming data collection and requesting them to fill in the web-based questionnaires. If the questionnaires are not completed, the patient will receive a reminder after 1 and 2 weeks. After 2 weeks, non-responders will be contacted by phone.

**Table 1 T1:** Participant timeline schedule

Table	Visit plan and case report forms											
	Intake	Surgery (t_0_)	1–2 day(s) following surgery	FU 3 weeks	FU 6 weeks	FU 3 months	FU 6 months	FU 12 months	FU 18 months	FU 24 months	FU 36 months	FU 48 months
Visit surgeon	x				x							
Research nurse visit	x				x			x		x		x
Randomisation		x										
Surgery		x										
Discharge			x									
Physical examination	x				x			x		x		x
Functional X-rays	x				x					x		
Roland-Morris Questionnaire	x			x	x	x	x	x		x	x	x
Oswestry Disability Index	x			x	x	x	x	x		x	x	x
NRS leg and back pain	x			x	x	x	x	x		x	x	x
Patient self-received recovery and satisfaction	x			x	x	x	x	x		x	x	x
EuroQol-5D	x			x	x	x	x	x		x	x	x
Cost questionnaires	x			x	x	x	x	x	x	x		
Short form 36	x			x	x	x	x	x		x	x	x
Revisit and complications	With occurrence											

FU, follow-up; NRS, Numeric Rating Scale.

### Data management

Data from initial visits to the hospital, follow-up visits and questionnaires will be entered into a database via an electronic data system (Gemstracker). This data will be noted and analysed by using coded information (study numbers) without any personal identifiers. Data will be stored via the secure data management system of the trial coordination centre of the Erasmus MC.

### Statistical analysis

Patient characteristics will be summarised per treatment group to determine whether the randomisation was balanced. Continuous variables will be presented using means and SDs, or in the case of non-normally distributed variables using medians and IQRs. Normality will be graphically assessed. Categorical variables will be presented using counts and percentages. The primary analysis will study differences in the primary outcome measure (RMDQ). The primary endpoint of interest is 12 months after randomisation. The results of the RMDQ will be assessed using generalised linear mixed models (GLMM), to account for the repeated measurements within patients and the multicentre stratification.

The secondary outcomes (ODI, NRS leg and back pain score, TUG test, TCST and the SF-36) will be similarly assessed using GLMMs and will be analysed for exploratory purposes. In all analyses the primary assessment of treatment effect will be the estimate of the main effect within the appropriate model at 12 months, adjusted for the stratification factors and main covariates. Time to recovery will be analysed using survival analysis (Cox proportional hazards). At 24, 36 and 48 months, the GLMM repeated-measurement analyses using the compound symmetry covariance structure will be used while *group* (interarcuair and conventional), *time* (moments of measurement) and the *interaction* between group and time (grou×time) will be entered as independent variables. Dependent variables are the primary and secondary outcome parameters. Likert scales for self-reported patient recovery and satisfaction will be assessed using descriptive statistics (counts and percentages) and appropriate plots. Comparisons of Likert scale results at individual time points will be tested using Mann-Whitney U tests. Complications and incidence of reoperations will be assessed using descriptive statistics (counts and percentages). Comparisons between treatment groups for specific complications of interest will be assessed using Χ^2^ tests or Fisher’s exact tests. If necessary, missing data will be imputed using multiple imputation techniques.

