### Sample size

The sample size of this study is calculated for the primary endpoint of group difference in the RMDQ at 12 months. According to literature, results obtained after interarcuair decompression should be 3 points lower on the RMDQ compared with those for the laminectomy group in order to detect superiority.^45^

Hence, the sample size of this study is based on a superiority design, using a delta of 3, an assumed true mean difference of 0 and a pooled SD of 6. Using an alpha of 0.05, and a power of 90%, we calculated a sample size of 69 patients per group. Accounting for a 20% loss in follow-up, we will therefore enrol 174 patients (87 patients per group).

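### The primary treatment effect is worded as a model main effect, which need not be the 12-month RMDQ difference on which the trial is sized

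*Protocol article*

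**What the plan says.** The Sample size section of the protocol article fixes the target: "The sample size of this study is calculated for the primary endpoint of group difference in the RMDQ at 12 months". It works "using a delta of 3, an assumed true mean difference of 0 and a pooled SD of 6", with alpha 0.05 and 90% power, and states: "we calculated a sample size of 69 patients per group". The Statistical analysis section also names 12 months as the primary endpoint.

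That section then chooses a longitudinal model: "The results of the RMDQ will be assessed using generalised linear mixed models (GLMM), to account for the repeated measurements within patients". The same model is meant to allow for stratification by centre. For all analyses it states that "the primary assessment of treatment effect will be the estimate of the main effect within the appropriate model at 12 months", adjusted for stratification factors and main covariates.

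Group, time and their interaction are listed as model terms only for the analyses at 24, 36 and 48 months. For the 12-month analysis the article does not say whether there is an interaction or how time is coded. It also does not say whether the words 'at 12 months' mean a contrast at that visit or a model fitted to the data up to that visit. Under Data collection methods and Table 1, the RMDQ is collected at baseline and at five postoperative visits up to 12 months: 3 weeks, 6 weeks, 3 months, 6 months and 12 months.

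**The concern.** A main effect of group in a repeated-measures model is not tied to a time point by its name.

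- Without a group-by-time term, it is a single group difference pooled over all visits in the model.
- With the interaction, it is the difference at the reference visit under reference coding, or an average over visits under other codings.

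It is the 12-month difference only if the effect is the same at every visit or 12 months is the reference visit. The article states neither. Because the interaction is spelled out only for the later analyses, a primary model without it is a natural reading.

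What is at stake is the headline result. If the groups separate late, a pooled effect understates the 12-month difference and loses power. If one group recovers faster and the other catches up, a pooled effect could be reported as a 12-month benefit when none exists at 12 months. Two analysts could also run different models with different answers, and each could claim to have followed the plan. The sentence covers all analyses, so the mixed-model secondary outcomes inherit the same ambiguity.

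**Working it through.** **Step 1. Reproduce the plan's figure.** Inputs from the Sample size section: difference 3, SD 6, alpha 0.05, power 90%, 20% loss. Allocation is 1:1 (Allocation section).

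n per group = 2 × SD² × (z_alpha + z_power)² / difference²

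- One-sided 0.05: 2 × 36 × (1.645 + 1.2816)² / 9 = 68.5, so 69.
- Two-sided 0.05: 2 × 36 × (1.960 + 1.2816)² / 9 = 84.1, so 85.
- Loss to follow-up: 69 / 0.80 = 86.25, so 87 per group and 174 in total.

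The stated 69 and 174 reproduce as a single-time-point comparison with one-sided alpha 0.05. The article does not state sidedness, which is a separate matter. What counts here is that the sample size rests on the standard error of one visit, not of an average.

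**Step 2. Standard errors of the two candidate quantities.** Assumptions not in the article: SD 6 at every visit, compound-symmetric within-patient correlation r = 0.5, equal weight to the five postoperative visits, and 69 per group with complete data.

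- 12-month contrast: 6 × √(2/69) = 1.02.
- Five-visit average: √[36 × (1 + 4r)/5 × 2/69] = √[36 × 3/5 × 2/69] = 0.79.

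**Step 3. What each quantity estimates, and how often it is significant.** Power = Φ(difference/SE − 1.96), two-sided 5%. The profiles are invented to show direction and are not predictions. Differences are listed in visit order.

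| Differences at the five visits | Average | Average significant | 12-month difference | 12-month contrast significant |
|---|---|---|---|---|
| 0, 0, 1, 2, 3 | 6/5 = 1.2 | Φ(1.2/0.791 − 1.96) = 33% | 3 | Φ(3/1.022 − 1.96) = 84% |
| 3, 3, 2, 1, 0 | 9/5 = 1.8 | Φ(1.8/0.791 − 1.96) = 62% | 0 | 5% (nominal level) |
| 3, 3, 3, 3, 3 | 15/5 = 3.0 | Φ(3/0.791 − 1.96) = 97% | 3 | 84% |

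**Step 4. Sensitivity to the assumptions.** With r from 0.4 to 0.8, the SE of the average runs from √[36 × 2.6/5 × 2/69] = 0.74 to √[36 × 4.2/5 × 2/69] = 0.94. The two-sided figure for the growing profile then runs from 37% down to 25%, and for the fading profile from 69% down to 49%.

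With one-sided 5% (1.645 in place of 1.96) and r = 0.5, the growing profile gives 45% for the average against 90% for the 12-month contrast. The fading profile gives 74% for the average.

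The averages of 1.2, 1.8 and 3.0 depend on neither the correlation nor the sidedness.

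**The case against.** The strongest reply is that the sentence itself ends with 12 months. The abstract, the Sample size section and the Statistical analysis section all name that time point, and nothing in the article defines an average over visits. A model with the interaction and 12 months as the reference visit has a group coefficient that is exactly the intended difference. This stands. A reader might infer that the planned primary analysis definitely does not estimate the 12-month difference, and the article does not support that.

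A second reply is that time coding and contrasts belong in an analysis plan that is not shown. That would answer a complaint about silence. Here, though, the article itself names the estimator, and the name it uses does not identify the quantity on which the trial is sized.

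A third reply is that the power figures are constructed. This also stands: they rest on invented profiles, an assumed correlation, equal visit weights and a two-sided level that the article does not state. A reader might also take the instability hypothesis in the Introduction as evidence that the difference grows during the first year. The article does not say so, and its own limitations list warns that instability may not be measurable within 2 years. If the effect is constant, averaging targets the same 3 points with better precision.

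**Conclusion.** The point holds as an ambiguity in the primary estimator, not as a proven mismatch. The stated target is the RMDQ difference at 12 months. The stated estimator can reasonably be run as a visit-averaged or reference-visit difference, which equals the target only under conditions that the article does not state.

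The possible error goes either way. In the illustrations, the average is 1.2 points when the 12-month difference is 3, and 1.8 points when it is 0. The first costs power (33% against 84%). The second gives a significant result in 62% of trials with no 12-month difference. These figures are conditional on SD 6, 69 per group, correlation 0.5, equal weights and two-sided 5%, and they show scale only. With a constant effect there is no bias.

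The wording governs the trial's main result and costs almost nothing to repair, so it should be settled before the analysis.

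**What to change.** Replace the reference to a main effect with: 'The primary treatment effect is the adjusted between-group difference in RMDQ at the 12-month visit, estimated as the 12-month contrast from a mixed model with group, categorical visit, group-by-visit, baseline RMDQ and centre.' Use the same visit-specific contrast for the secondary outcomes analysed with mixed models, and report any visit-averaged effect as supportive.

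The cost is one sentence and one contrast statement. Data collection and, for this point, the sample size stay as they are. The downside is a larger standard error than the average if the effect is in fact constant: about 1.02 against 0.79 points under the assumptions above. The 1.02 is the standard error that the sample size already assumes, so the planned power for the 12-month difference is not reduced.

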### Economic evaluation

An economic evaluation will be performed from the societal and healthcare perspectives to evaluate the cost-effectiveness of the bilateral interarcuair decompression compared with a ‘classic’ laminectomy for patients with INC. When the societal perspective is applied, all costs and consequences relevant to the interventions will be taken into account, whereas only costs accruing to the formal Dutch healthcare sector will be considered when the healthcare perspective is applied. Intervention costs will be estimated using a micro-costing approach. Cost questionnaires will be administered at 3, 6 and 12 weeks covering the entire period and at 6, 12, 18, 24, 36 and 48 months after surgery covering the previous 3 months. Data will be collected on healthcare utilisation, the use of informal care, absenteeism, presenteeism and unpaid productivity losses. Costs will be valued using guideline prices recommended in the Netherlands.^46^

A cost-utility analyses will be conducted with QALYs as outcome. For estimating QALYs, the patients’ EQ-5D-5L health states will be converted into utility scores using the Dutch tariff.^43^ Linear interpolation between measurement points will be used to subsequently calculate QALYs. Missing data will be imputed using multiple imputation by chained equations.^47^ An incremental cost-utility ratio will be calculated by dividing the difference in costs by the difference in effects. The cost-utility ratio expresses the incremental costs per QALY gained. Bootstrapping techniques will be used to estimate the uncertainty surrounding the cost-effectiveness estimates. Uncertainty will be shown in cost-effectiveness planes and cost-effectiveness acceptability curves, and sensitivity analyses will be performed to test the robustness of the study results.

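### Pre-operative RMDQ and EQ-5D are collected, but the 24–48 month models and the QALY difference are set out without them, and their role at 12 months is not stated

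*Protocol article*

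**What the plan says.** **Collection.** Data collection methods states: "All patient reported outcomes will be collected preoperatively". Table 1 marks both the RMDQ and the EuroQol-5D in the intake column.

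**Mixed models.** Statistical analysis uses generalised linear mixed models for the RMDQ, to allow for repeated measurements and the multicentre stratification. It then says that, across analyses, the 12-month estimate will be "adjusted for the stratification factors and main covariates". The only stratification factor is centre (Allocation: "Variable block sizes of 4, 6 and 8 will be used and stratified by treatment centre"). No main covariate is named. For 24, 36 and 48 months the same section gives a compound-symmetry model and lists its independent variables as group, time and group×time. Neither a pre-operative value nor centre is on that list.

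**Cost-utility.** Economic evaluation computes QALYs by linear interpolation of EQ-5D-5L utilities and then says: "An incremental cost-utility ratio will be calculated by dividing the difference in costs by the difference in effects". It specifies chained-equation imputation, bootstrapping and sensitivity analyses. It mentions no adjustment for baseline utility.

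**The concern.** The text leaves three uses of the pre-operative RMDQ open: as a covariate, as the first of the repeated responses, or not at all. These are different analyses. If it is just another response time in a model with group, time and group×time, then with complete data the 12-month contrast equals the plain difference in 12-month means, and nothing is gained from baseline. For 24–48 months the listed terms point to an analysis without baseline or centre, which sits badly beside the adjustment sentence.

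In the economic part, patients who start with higher utility can be expected to have higher utility later. A chance difference between groups at intake therefore carries through into the QALY difference. That difference is the denominator of the ratio, where small absolute shifts can matter. Cost-effectiveness is the stated secondary objective. Bootstrapping shows this noise but does not remove it.

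**Working it through.** **Inputs from the article (Sample size).** Difference and spread: "using a delta of 3, an assumed true mean difference of 0 and a pooled SD of 6". The significance level is 5% with sidedness not stated, the target power is 90%, the result is 69 per group, and 20% loss to follow-up brings the total to 174.

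**Assumptions, not in the article.** Correlation ρ between pre-operative and 12-month RMDQ: 0.2 to 0.5. Utility SD: 0.15 to 0.25. Slope of one-year QALY on baseline utility: 0.2 to 0.6.

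**Step 1: reproduce the plan's figure.** n per group = 2σ²(z_α + z_β)²/δ² = 2·36·(z_α + 1.2816)²/9 = 8(z_α + 1.2816)².

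- One-sided 0.05: 8(1.6449 + 1.2816)² = 68.5, so 69. This matches.
- Two-sided 0.05: 8(1.9600 + 1.2816)² = 84.06, so 85. This does not match.
- Drop-out: 69/0.8 = 86.25, so 87 per group and 174 in total. This matches.

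**Step 2: power with and without baseline.** Adjustment reduces the residual SD to 6√(1−ρ²). Power = Φ(3/[6√(1−ρ²)·√(2/69)] − z_α). At ρ = 0 the first term is 3/(6 × 0.1703) = 2.937.

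| ρ | Residual SD | Two-sided 5% | One-sided 5% |
|---|---|---|---|
| 0 | 6.00 | 83.6% | 90.2% |
| 0.2 | 5.88 | 85.0% | 91.2% |
| 0.3 | 5.72 | 86.8% | 92.4% |
| 0.4 | 5.50 | 89.3% | 94.1% |
| 0.5 | 5.20 | 92.4% | 96.0% |

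These are normal approximations. The t-based values at ρ = 0 are 83.0% and 89.9%. With a two-sided test, 90% is reached at ρ = √(1 − 69/84.06) ≈ 0.42.

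**Step 3: QALY difference.** The standard error of a chance baseline utility difference is SD·√(2/n).

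- Smallest case: 0.15·√(2/87) = 0.0227; times slope 0.2 gives about 0.005.
- Largest case: 0.25·√(2/69) = 0.0426; times slope 0.6 gives about 0.026.

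A one-standard-error imbalance therefore moves the unadjusted one-year QALY difference by about 0.005–0.026. The first follow-up is at 3 weeks, so the direct interpolation weight of the intake value is only ½ × 3/52 = 0.029 year, worth at most 0.0426 × 0.029 ≈ 0.001 QALY. Almost all of the shift comes through correlation with later utility.

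**The case against.** The strongest reply is that a journal article condenses the plan. Naming covariates and giving the regression form for incremental QALYs are commonly left to a statistical analysis plan, and one may exist. For the 12-month model this largely stands. The article promises covariate adjustment, and the pre-operative RMDQ may well be one of the unnamed covariates.

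For 24–48 months the reply is weaker, because the article does list the independent variables. One can argue that the adjustment sentence is tied to the 12-month estimate, or that centre enters as a random effect and so would not be listed. That makes the two statements an awkward fit rather than a flat contradiction. They still leave baseline out of the later models as written.

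On QALYs, the ratio sentence does not say how each difference is estimated, so it does not rule out adjustment. Chance imbalance under randomisation is also noise, not systematic bias, and the planned bootstrap, planes and acceptability curves will show it. Both remarks are correct. But the section sets out interpolation, imputation and bootstrapping without adjustment, and showing the noise is not the same as removing it.

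Finally, the gain rests on assumed correlations. That is true, and it is why ranges are given.

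**Conclusion.** The point holds as a free improvement. As written, the 24–48 month models omit the pre-operative value and centre, the QALY difference has no baseline-utility adjustment, and the role of the pre-operative RMDQ at 12 months is unspecified. At 69 completers per group, and for ρ between 0.2 and 0.5, adjustment adds about 1.5 to 9 percentage points of power with a two-sided test, or about 1 to 6 with a one-sided test. For QALYs it removes a chance shift of about 0.005–0.026 per standard error of imbalance, given the assumed utility SD, group size and slope.

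A reader might infer more, and the article does not support it:

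- **That baseline RMDQ is excluded from the primary model.** The text promises covariate adjustment and does not exclude it.
- **That leaving it out causes a power shortfall.** The planned 69 per group reproduces at one-sided 0.05, where the unadjusted analysis already has about 90%. The figure of about 83% arises only if the test is two-sided. Its source is then the sidedness left unstated under Sample size, not a missing baseline term.
- **That the unadjusted cost-utility ratio is biased by design.** Adjustment here corrects chance imbalance, not a systematic error.

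**What to change.** In Statistical analysis, state that every mixed model for a continuous outcome, at 12 months and at 24–48 months, includes the pre-operative value of that outcome and centre as covariates. Name any further main covariates before outcome data are examined. Bring the 24–48 month term list into line with the adjustment sentence.

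In Economic evaluation, state that incremental QALYs are estimated by regression on group, baseline EQ-5D utility and centre, with this regression run inside each bootstrap replicate.

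The cost is two or three sentences in the protocol or analysis plan. The values are already collected at intake, so no new data, visits or patients are needed. Missing intake values can be handled by the multiple imputation already foreseen.

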## Introduction

Lumbar spinal stenosis (LSS) is described as the narrowing of the diameter of the spinal and nerve root canals, which can cause compression of the neural structures in the canals.^1^ LSS is a common medical condition in the ageing population and is considered the most common reason for lumbar spine surgery for people over the age of 65.^2–4^ Intermittent neurogenic claudication (INC) is the most important symptom of LSS, with leg pain and heaviness of the legs, usually bilateral, which exacerbate during standing and walking. Apart from leg pain, back pain is often also present.^5^ As the symptoms aggravate, the ability to walk can become considerably limited, which is the dominant functional impairment and the most common reason for seeking medical care.^6 7^

Conservative treatment, such as physical therapy and pain medication, is the first treatment option and may give some relief of symptoms.^8^ Previous research shows that there is sparse evidence of the effectiveness of surgery compared with non-operative treatment.^9^ However, usually when conservative treatment fails, surgical treatment is considered the next option.^10 11^ The first technique described to widen the lumbar spinal canal is the laminectomy technique, also known as wide bony decompression, which is a widely used surgical technique for patients with INC caused by LSS.^12^ Given that patients often experience postoperative back pain after laminectomy, it is hypothesised that laminectomy is a ground for potential lumbar instability and iatrogenic scoliosis.^13–15^ Performing a procedure with potentially more complications in an elderly population could be considered as doubtful. Hence, less invasive techniques, such as the bilateral small size interarcuair decompression, otherwise known as a bilateral laminotomy, limited bony decompression or interlaminar decompression, were developed and implemented in clinical practice. These techniques require less bone tissue to be removed, which possibly can reduce the prevalence of lumbar instability in these patients and consequently improve functioning.^16^ Furthermore, it is believed that, compared with laminectomy, these less invasive techniques have the ability to decompress the nerves while preserving the spinal integrity. However, the risk of an insufficient decompression may be higher, possibly resulting in reoperations due to residual stenosis.^16–18^

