##### Patients’ perceived recovery

Recovery will be measured using a 7-point Likert scale. The score on this scale varies from ‘complete recovery’ to ‘worse than ever’. The outcomes ‘complete recovery and ‘almost complete recovery’ will be dichotomised and considered as recovered.^32^

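### Cox regression is planned for recovery, a reversible state seen only at scheduled questionnaires, while reoperation, which has real dates, gets only counts and percentages

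*Protocol article*

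**What the plan says.** **Recovery.** Under Patients' perceived recovery: "Recovery will be measured using a 7-point Likert scale". The two best categories form the event: "The outcomes ‘complete recovery and ‘almost complete recovery’ will be dichotomised and considered as recovered". The section gives no rule for first or sustained recovery. Data collection methods lists the postoperative questionnaires at "3 weeks, 6 weeks, 3 months, 6 months, 12 months, 18 months, 24 months, 36 months and 48 months". Table 1 has no recovery assessment at 18 months, which leaves eight times, five of them in the first year. Under Statistical analysis: "Time to recovery will be analysed using survival analysis (Cox proportional hazards". The same section also gives the recovery scale counts, percentages and plots, and adds: "Comparisons of Likert scale results at individual time points will be tested using Mann-Whitney U tests".

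**Reoperation.** The Introduction says of the less invasive techniques that "the risk of an insufficient decompression may be higher, possibly resulting in reoperations due to residual stenosis". The section on complications and reoperation classes reoperation as a bad outcome. Table 1 records revisits and complications as they happen, in a schedule that runs to 48 months. The analysis is: "Complications and incidence of reoperations will be assessed using descriptive statistics (counts and percentages". The only tests nearby are limited in scope: "Comparisons between treatment groups for specific complications of interest will be assessed using Χ^2^ tests or Fisher’s exact tests". Reoperation is not named there.

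**The concern.** The survival method goes to the outcome whose event times are not observed, and is withheld from the one whose times are.

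A patient first rated recovered at the 12-month questionnaire became so at some point between 6 and 12 months. Continuous-time Cox regression assumes known event times with few ties. Here the gaps between assessments widen from 3 weeks to 12 months, and on nominal visit dates every event falls on one of eight values. The hazard ratio is then pulled towards 1, by an amount that depends on tie handling and date coding. Each answer is also a current state, so recovery can be lost again, and a single event time cannot show that.

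Reoperation has a date, and follow-up is long enough for patients to be lost. A crude percentage uses neither fact. At stake are the size of any recovery effect and a fair account of the main counter-risk of the intervention.

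**Working it through.** **Inputs from the article.** 87 patients per group after a planned 20% loss (69 / 0.8 = 86.25, rounded up to 87; 2 x 87 = 174), and the assessment times in Table 1. The article gives no figure of its own for recovery or reoperation, so there is none to reproduce.

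**Assumptions.** Exponential recovery times; control median of 6 or 13 weeks (also 26 weeks in the eight-visit runs); true hazard ratio (HR) of 1.0, 1.5 or 2.0. For reoperation: true 48-month risks of 5-20%, with 10% as the worked case, and exponential loss. The 20% loss is set by the article for the 12-month endpoint and is applied here to 48 months; 10% and 30% show the range.

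**Step 1: recovery, eight visits (3, 6, 13, 26, 52, 104, 156 and 208 weeks).** Each time is moved to the next visit and a Cox model is fitted, with 400 simulated trials per setting.

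| True HR | Exact times | Breslow ties | Efron ties |
|---|---|---|---|
| 1.0 | 0.99-1.01 | 0.99-1.01 | 0.99-1.01 |
| 1.5 | 1.52 | 1.33-1.36 | 1.47-1.48 |
| 2.0 | 1.99-2.03 | 1.58-1.68 | 1.88-1.93 |

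**Step 2: recovery, the five first-year visits, true HR 1.5.**

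| Analysis | Estimated HR | Power |
|---|---|---|
| Cox, Breslow, nominal dates | about 1.32-1.35 | about 40-50% |
| Cox, Breslow, response dates spread over 0-14 days | 1.42-1.47 | 63-69% |
| Cox, Efron, nominal dates | 1.45-1.47 | 66-69% |
| Discrete-time complementary log-log | 1.50-1.53 | 70-72% |

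The simulation was repeated several times. One repeat reached 1.37 (52%) for Breslow, 1.50 (71%) for Efron and 1.55 (74%) for complementary log-log, and the lowest Breslow power was 38%. With 300 trials, the Monte Carlo standard error at 70% power is sqrt(0.7 x 0.3 / 300) = 2.6 points, so differences of this order are noise. At a true HR of 1.0, Breslow rejected in 1-2% of trials at a nominal 5%, and Efron and complementary log-log in 5-6%. The error is therefore conservative.

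**Step 3: reoperation.** Let r be the true 48-month risk and d the proportion lost by 48 months. Set a = -ln(1 - r) and b = -ln(1 - d). If lost patients stay in the denominator, the crude proportion is a/(a + b) x [1 - exp(-(a + b))].

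- r = 0.10, d = 0.20: a = 0.1054, b = 0.2231; 0.3207 x (1 - 0.72) = 0.0898, or 9.0%.
- r = 0.10, d = 0.30: b = 0.3567; 0.2280 x (1 - 0.63) = 0.0844, or 8.4%.
- r = 0.10, d = 0.10: b = 0.1054; 0.5 x (1 - 0.81) = 0.0950, or 9.5%.

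At 20% loss, the ratio of crude to true risk is 0.897 for r = 5% and 0.900 for r = 20%. Equal loss therefore lowers both arms by about 10% in relative terms and hardly changes their ratio. With 10% loss in one arm and 30% in the other, equal true risks of 10% show as 9.5% and 8.4%, an apparent risk ratio of 8.4/9.5 = 0.89 made by follow-up alone.

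**Step 4: precision for reoperation.** At 10% there are 87 x 0.10 = 8.7 events per arm. The standard error of the log HR is about sqrt(1/8.7 + 1/8.7) = 0.48, so the 95% limits lie a factor of exp(1.96 x 0.48) = 2.6 either side of the estimate.

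**The case against.** The strongest reply is that Cox regression is nearly adequate here. The article names no software, tie method or date coding, and these may properly be left to an analysis plan. Questionnaires are web-based, with reminders after 1 and 2 weeks and then a telephone call, so actual response dates will spread. With that spread, or with Efron ties, Cox falls only a few points of power short of the discrete-time model. Both arms share one schedule and the null holds. All of this stands.

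Four stronger readings are tempting, and the article does not support them:

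- **That the recovery analysis is invalid or will lose a large part of its power.** That needs Breslow ties and nominal dates together, and the article prescribes neither.
- **That relapse is ignored.** The per-visit counts and Mann-Whitney tests use the current state, so lost recovery partly shows. The mixed-model analysis at 24 to 48 months takes primary and secondary outcomes as dependent variables and may be meant to include recovery.
- **That lost patients are counted as not reoperated.** No denominator is stated, and multiple imputation is allowed where needed. The understatement in step 3 is conditional on that denominator.
- **That the reoperation comparison is biased.** This requires loss that differs by arm, and nothing in the article suggests it.

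It can also be said that describing about nine events per arm is reasonable. The imprecision is real, but it does not justify leaving out timing and censoring. If reoperation were counted among the complications of interest, a chi-squared or Fisher test would leave them out as well.

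**Conclusion.** The point holds as a modest, worthwhile improvement to two secondary outcomes. The RMDQ analysis and the sample size are unaffected. The choice of method for each outcome is fixed in the article, so this is more than a detail awaiting an analysis plan.

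For recovery, the planned Cox model biases the hazard ratio towards 1. The bias is slight under sensible handling (a true 1.5 estimated at about 1.42-1.47) and substantial only with Breslow ties on nominal dates. These figures rest on exponential recovery times and the assumed control medians.

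For reoperation, the plan omits timing and censoring for the intervention's named counter-risk. Under an assumed 10% risk with lost patients kept in the denominator, the understatement is about 1 percentage point at 20% loss and 1.6 points at 30%. A distorted comparison follows only from unequal loss.

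**What to change.** **Recovery.** Define the event as first recovery. Analyse it with a discrete-time complementary log-log model over the visit intervals, which keeps the hazard-ratio interpretation, or with an interval-censored model. Report the proportion recovered over time from a repeated-measures logistic model, so that relapse counts. If Cox is kept as a supporting analysis, state Efron ties and which date is used.

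**Reoperation.** Report cumulative incidence by arm to 48 months, by Kaplan-Meier or with death as a competing event, censoring at last contact. Give a between-group estimate with 95% CI and say that few events will make it imprecise. Keep the counts alongside, with their denominators.

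**Cost.** Some wording and a little more analysis. No new data, visits or patients are needed.
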